European guidelines recently incorporated FeNO as an effective alternative and cost-effective diagnostic tool for asthma and to optimise access to specialised testing : a FeNO level ≥40 ppb is 90% specific for asthma diagnosis in adults.^29 30^ The United Kingdom’s National Institute for Health and Care Excellence (NICE) guidelines recommend using FeNO and BEC early in the diagnostic algorithm as a first-line diagnostic tool before spirometry or peak flow monitoring.^29 30^ In children ≥5 years, only FeNO (≥35 ppb) has been validated as a first-line diagnostic test, while BEC had been used after BDR and PEF, along with skin prick tests or specific IgE measurement.^29 31^ The introduction of FeNO testing as a first-line diagnostic tool is estimated to enable approximately 29 000 additional asthma diagnoses annually, leading to earlier treatment initiation, improved disease control, reduced absenteeism and potential cost savings of £100–204 million per year.^32^

In Quebec, over 3000 diagnostic tests are still pending across Centre Hospitalier Universitaire de Sherbrooke (CHUS), CHU Sainte-Justine (CHUSJ) and the Montreal Children’s Hospital (MHC), including 1300 tests for children, with wait times exceeding 1 year. BPTs are scheduled chronologically, with priority only for internal referrals, that is, for specialists of the institution. The lack of robust prospective data on FeNO and eosinophils (and limited FeNO access) has restricted their integration into diagnostic algorithms.

Our overarching aim is to address an evidence gap by evaluating the integration of inflammatory biomarkers into referral for the asthma diagnosis specifically from primary or community care under real-world conditions. Specifically, we aim to assess whether FeNO and BEC can improve the prioritisation of patients for bronchial provocation testing (BPT), thereby streamlining referrals and supporting more timely and cost-effective asthma diagnosis. Propulsion Santé also includes two translational sub-studies: DIVE (in adults) and DIVE-2 (in children) involving additional sampling (serum and nasal epithelial lining fluid (NELF)) to link inflammatory mediators (alarmins, interleukins and eicosanoids), diagnosis and T2 biomarkers to gain mechanistic insight at the point of diagnosis in primary care.

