### Participants

Eligible participants are individuals aged ≥6 years who present with symptoms suggestive of asthma and have been referred by primary care (family physicians and nurse practitioners) or community practice (eg, paediatricians and other non-pulmonologist physicians) for asthma diagnosis at one of the three participating centres. Participants are identified from an existing waiting list of approximately 3000 patients awaiting respiratory function testing. The only exclusion criterion for PROPULSION SANTÉ is refusal to participate in the study.

Among these patients, a target sample of 123 adult participants (aged≥18 years) and 123 paediatric participants (aged 6–18 years) undergoing BPT will be consecutively invited to participate in the DIVE and DIVE-2 sub-studies, respectively, regardless of their T2 status. DIVE/DIVE2 inclusion requires non-diagnostic spirometry and no contraindication to methacholine challenge. Patients will be excluded from participation if they meet any of the following conditions: use of inhaled or systemic corticosteroids within 48 hours prior to testing; tobacco use within the previous 6 hours; diagnosis of chronic obstructive pulmonary disease (COPD), defined as all of the following — age ≥40 years, fixed airway obstruction on spirometry (FEV1/Forced Vital Capacity (FVC)<0.7) and a smoking history >10 pack-years or documented alpha-1 antitrypsin deficiency— and evidence of parenchymal lung disease (such as cystic fibrosis or bronchiectasis), unstable cardiac disease or a history of acute respiratory infection (viral or bacterial) within the preceding 4 weeks.

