### Outcomes measures

#### Primary Outcome

The primary outcome, diagnostic delay, will be defined as the interval between primary care requisition for pulmonary function testing and the last confirmatory diagnostic test conducted (BDR or BPT). This continuous outcome will be analysed longitudinally and stratified by biomarker-guided diagnostic strategies, also adjusting for the time of inclusion in the study. Sensitivity analyses will also examine diagnostic delay for FeNO and blood eosinophils considered separately.

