For the primary outcome of waiting time differences, the baseline diagnostic delay, prior to the project implementation, will be established based on the time elapsed between the initial request for an asthma diagnostic test made by primary care and the performance of that test. During the intervention, diagnostic delays will be monitored prospectively, both overall and stratified by inflammatory status. We will apply linear mixed-effects models with restricted maximum likelihood estimation. These models will incorporate (high-risk vs low-risk), study period at time of inclusion, and the number of awaiting tests as fixed effects. Random effects will account for within-centre clustering and repeated measurements. In addition, Kaplan-Meier survival curves will be constructed to visualise the probability of remaining undiagnosed over time for both high-risk and low-risk inflammatory phenotypes. These curves will allow for a graphical representation of differences in diagnostic efficiency between groups. Cox proportional hazards regression will be used to identify significant predictors of waiting time with HRs and 95% CIs reported.

Diagnostic performance in the secondary outcome will be evaluated through ROC analysis, calculating the area under the curve (AUC) with 95% CIs for each individual marker and for their combined use. Sensitivity, specificity, positive and negative predictive values and likelihood ratios will be calculated with their respective 95% CIs.

Health utility values will be derived from EQ-5D questionnaires^39 52 53^ completed at baseline and follow-up visits. Quality-adjusted life years will be calculated using the AUC method, connecting utility values across measurement time points. This approach integrates health-related quality of life over the 12-month follow-up period. To assess the financial implications of implementing FeNO testing within the provincial healthcare framework, we will develop a budget impact model for the MSSS. Environmental and satisfaction-related outcomes will be analysed using descriptive statistics. CO₂ emissions from inhalers dispensed to non-asthmatic individuals will be estimated based on Cascades Canada data,^27^ and patient satisfaction with inflammometry will be assessed using structured questionnaires.

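### In the overall comparison with the pre-implementation baseline, a substantial part of the delay counted as intervention-period delay accrued before launch, because period is taken at inclusion while the clock starts at requisition

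*Protocol article*

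**What the plan says.** All locations are in the protocol article.

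- **Source of participants** (Participants): "Participants are identified from an existing waiting list of approximately 3000 patients awaiting respiratory function testing". The Sample size section also counts on expected referrals, without giving their share.
- **State of that list** (Introduction): about 3000 tests are pending, "including 1300 tests for children, with wait times exceeding 1 year". On scheduling: "BPTs are scheduled chronologically, with priority only for internal referrals".
- **Outcome clock** (Primary Outcome): delay starts at the primary care request and ends at the last confirmatory test. It does not restart at launch or at inclusion. The analysis is described as "also adjusting for the time of inclusion in the study".
- **Before period** (Statistical methods): "the baseline diagnostic delay, prior to the project implementation, will be established based on the time elapsed" between the primary care request and performance of the test.
- **Intervention period** (Statistical methods): "During the intervention, diagnostic delays will be monitored prospectively, both overall and stratified by inflammatory status".
- **Model** (Statistical methods): a linear mixed model with risk group, "study period at time of inclusion, and the number of awaiting tests as fixed effects". Kaplan-Meier curves by risk group and Cox regression are also planned.

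**The concern.** The clock is tied to the request date, whereas the period label is tied to the inclusion date. For someone already on the list at launch, the two fall on opposite sides of the launch date. A patient referred 12 months before launch and tested in month 1 contributes a delay of 13 months to the intervention period, and 12 of those months were spent under the old system.

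Nothing in the text splits the interval at launch, restarts the clock, uses delayed entry or classifies patients by request date. The number of awaiting tests describes the queue. It does not separate one patient's waiting before launch from waiting after it.

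The overall change from baseline is at stake. It could understate a real shortening of the wait. It could also move with the order in which the convenience sample is drawn from the list, even if the service has not changed.

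**Working it through.** The plan gives no figure for this quantity, so there is none to reproduce. The stated sample size does not bear on it.

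**Inputs from the article:** a 12-month recruitment window (Sample size), waits above 1 year and chronological booking (Introduction), and a clock running from request to final test (Primary Outcome).

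**Assumptions:** total wait W of 12 to 18 months, since the article says only that waits exceed a year; testing spread evenly over months t = 0 to 12 after launch; a speed-up factor k; and the share p of new referrals.

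**1. Constant wait.** A patient tested at month t waited W − t months before launch. The mean pre-launch share is 1 − mean(t)/W = 1 − 6/W.
- W = 12: 1 − 6/12 = 50%
- W = 15: 1 − 6/15 = 60%
- W = 18: 1 − 6/18 = 67%

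**2. Chronological queue with testing k times faster from launch.** The patient tested at t was requested at kt − W. The delay is therefore W − (k − 1)t, of which max(W − kt, 0) precedes launch. With k = 1.5, summed over t = 0 to 12:
- W = 12: pre-launch waiting runs to t = 8 and sums to 12×8 − 0.75×8² = 48. Total delay is 12×12 − 0.25×12² = 108. Share 48/108 = 44%.
- W = 18: pre-launch waiting is 18×12 − 0.75×12² = 108. Total delay is 18×12 − 0.25×12² = 180. Share 108/180 = 60%.

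**3. Effect on the measured change in the same queue.** Mean delay among patients tested in the year is W − 6(k − 1). A request made at launch waits W/k.

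| k | W (months) | Mean delay (months) | Measured fall | Fall for a request made at launch |
|---|---|---|---|---|
| 1.5 | 12 | 9.0 | 25% | 33% |
| 1.5 | 18 | 15.0 | 17% | 33% |
| 1.25 | 12 | 10.5 | 12.5% | 20% |
| 1.25 | 18 | 16.5 | 8% | 20% |

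**4. New referrals.** Suppose listed patients had waited 12 months at launch and wait 6 more on average, and new referrals wait 6 months. The pooled pre-launch share is 12(1 − p) / [18(1 − p) + 6p].
- p = 0: 12/18 = 67%
- p = 0.25: 9/15 = 60%
- p = 0.5: 6/12 = 50%

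**5. Sampling order.** Steps 2 and 3 assume chronological testing. If the convenience sample favoured recent requests, a patient who had waited 2 months at launch and was tested in month 1 would record 3 months. Against a 12-month baseline this looks like a large gain when only the order has changed. Taking the longest waiters first does the opposite.

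**The case against.** **No before-after test is written out.** The article says that a baseline will be established and delays monitored. Pre-implementation patients have no biomarker result and no inclusion date, so they do not fit the mixed model as written, and the period term could simply mean calendar time within the study. Exact coding is often left to a fuller document. This stands in part: the comparison is implied, not specified. However, the article puts the baseline under the primary outcome and itself pairs a requisition clock with an inclusion-based period. If the two delays are compared on those terms, the carry-over follows.

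**The headline contrast is high versus low risk.** This stands. The Abstract defines the primary outcome that way and both groups carry the wait before inclusion, so that difference is less affected. A reader might infer that the primary contrast itself is mostly old-system waiting time compared with old-system waiting time; the documents do not support carrying the before-after bias over to it.

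**The baseline is not the only usual-care reference.** This also stands. Under Intervention, low-risk patients with non-diagnostic spirometry have their provocation test booked from the standard list. They form a concurrent, non-randomised usual-scheduling group.

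**The size is uncertain and the illustration models throughput.** Both are fair. The speed-up in steps 2 and 3 is a change in testing rate, not the effect of reordering by biomarker, so no bias is computed for prioritisation itself. The comparison value is also a choice: with k = 1.5 and W = 12, the patient tested at month 12 waits 12 − 0.5×12 = 6 months, a 50% fall, against 33% for a request made at launch.

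**Conclusion.** The point holds for the overall comparison with the pre-implementation baseline. A substantial part of the delay labelled as intervention delay accrued before launch, and neither period at inclusion nor the number of awaiting tests removes it. The share is about 50% to 67% at constant waits of 12 to 18 months and about 44% to 60% with a 1.5-fold speed-up. It falls as more participants are new referrals. Waits, speed-up, even testing and referral share are all assumptions.

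A reader might infer that most of the intervention delay is old-system waiting. That is not assured: the share is exactly half at a constant 12-month wait and 44% in the 12-month queue with a 1.5-fold speed-up. Nor is the direction of the bias fixed. It is toward no effect under roughly chronological testing, but recruitment is by convenience sampling and another order can reverse it.

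**What to change.** **Overall comparison with baseline.** Assign waiting time, not patients, to periods.
- Use a time-to-test model with time since requisition as the time scale, split at each centre's launch date.
- Censor patients still waiting at launch for the baseline period, and let them enter the intervention period by delayed entry at the waiting time already reached.
- Keep listed patients not yet tested in the data as censored.
- Use this time-varying period term in place of study period at inclusion for this comparison.
- Label mean delays of patients requested before launch as descriptive.

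Restricting the comparison to requests made after launch, without censoring, is not a substitute. Anyone requested and included within the 12-month window has waited less than 12 months at inclusion by construction.

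**High versus low risk.** Do not apply the launch split to the risk-group Kaplan-Meier curves, because risk status is known only from the biomarker visit. Start follow-up at that visit and end it at the final test.

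**Cost.** Cox and Kaplan-Meier methods are already planned, and request and test dates are already needed to establish the baseline. The additions are analysis wording, extraction of list dates for patients still waiting, and slightly lower precision.

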### Intervention

The interpretation of respiratory function tests and biomarkers will be performed by the principal investigator pulmonologist at each centre or by trained designated collaborating pulmonologists by following these models:

High-risk inflammatory asthma is defined by FeNO ≥25 ppb or BEC ≥300 cells/µL in participants ≥12 years (≥20 ppb or ≥300 cells/µL in children aged 6 to <12 years)^15 50^ : one or more elevated biomarkers will be interpreted as a high risk of asthma exacerbation. If spirometry is non-diagnostic, BPT will be prioritised (<2–4 weeks).Low risk inflammatory asthma is defined by FeNO <25 ppb and BEC <300 cells/µL (<20 ppb or <300 cells/µL in children aged 6–<12 years)^15 50^: this will be interpreted as a low risk of asthma exacerbation. If spirometry is non-diagnostic, BPT will be scheduled according to the standard waiting list.

Results of biomarkers will be integrated on the medical report indicating the probability (high/low) of asthma exacerbation and suggested management with either ICS taken as-needed (T2-low) or regularly (T2-High) ICS if clinically appropriate, which will be forwarded to the referring physician.

The patient test pathway based on their respiratory test and the results of the inflammometry assessment is summarised in figure 2.

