### Statistical methods

Data will be independently analysed by a biostatistician from the CHUS using R software (V. 4.2.0 or later, R Foundation for Statistical Computing, Vienna, Austria) in collaboration with a health economist. Missing data will be documented, and multiple imputation by chained equations will be considered for data missing at random when <20% of data is missing. Statistical significance will be determined using a two-sided alpha level of 0.05. Adjustments for multiple comparisons with the Benjamini-Hochberg procedure will be applied where necessary, including for subgroup analyses on the primary outcome.^51^

All primary analyses will also be stratified by pre-specified subgroups: study site, age categories (6–<12 years, 12–<18 years, ≥18 years), biological sex, ethnicity, smoking status and other potential confounding variables related to inflammatory biomarker measurement. Additionally, we will perform sensitivity analyses excluding active smokers. Categorical variables will be presented as counts with corresponding percentages, while continuous variables will be reported as either means with standard deviations (for normally distributed data) or medians with interquartile ranges (for non-normally distributed data). For comparative analyses between groups, we will employ independent t-tests or Mann-Whitney U-tests for continuous variables based on distribution, and χ^2^ tests or Fisher’s exact tests for categorical variables, as appropriate based on expected cell frequencies.

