### Sample size

Approximately 3000 diagnostic tests for suspected asthma are currently pending across the three participating centres (CHUS, CHUSJ and MCH), including around 1500 paediatric tests. Propulsion Santé was funded for 12 months of full-time recruitment (convenience sampling). Based on this pre-existing waitlist and expected referral rates, the Propulsion Santé study aims to recruit 1500 participants aged 6 years and older in the three centres. This sample size will allow us to detect a minimal effect size of 0.07 (Cohen’s f), assuming a significant level of 5%, a power of 80% and a correlation of 0.5 among repeated measures. The calculation was performed using a power analysis for a repeated measures ANOVA with a between-subjects factor in G*Power v 3.1.9.4. Of course, this sample size exceeds our minimum requirement, providing greater assurance in detecting the expected effects, but will also provide a unique opportunity to evaluate diagnostic delays and outcomes in real-world conditions. In addition, the findings will contribute to an ongoing meta-analysis on the diagnostic performance of inflammatory biomarkers.^54^

For the DIVE and DIVE 2 translational substudies (designed prior to PROPULSION SANTÉ), a sample size of 123 participants was originally calculated to provide 90% power to assess the diagnostic performance of three ROC curves. The sample size assumes a 2:1 ratio of asthma-positive to asthma-negative participants, allowing the analysis of three ROC curves, each targeting area under the curve (AUC) values ≥ 0.7, which are significantly different from the null hypothesis (AUC = 0.5), using a two-sided alpha level < 0.016, adjusted for multiple comparisons across three biomarkers.

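### The lead model for diagnostic delay can use only completed delays, so any provocation test still pending at analysis pulls the high-versus-low difference towards zero, by an amount that depends on an unstated data cut

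*Protocol article*

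**What the plan says.** The Primary Outcome section defines diagnostic delay as "the interval between primary care requisition for pulmonary function testing and the last confirmatory diagnostic test conducted (BDR or BPT". It adds: "This continuous outcome will be analysed longitudinally and stratified by biomarker-guided diagnostic strategies".

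The Statistical methods section names its lead model for this outcome: "We will apply linear mixed-effects models with restricted maximum likelihood estimation". The fixed effects are risk group, study period at inclusion and number of pending tests. Two methods that can handle censoring follow. One is introduced with "In addition, Kaplan-Meier survival curves will be constructed to visualise the probability of remaining undiagnosed over time", by risk group. The other is a Cox regression, described as a way to find predictors of waiting time.

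The Intervention section treats the groups differently by design. After non-diagnostic spirometry, high-risk patients get BPT within about 2–4 weeks. For low-risk patients, "BPT will be scheduled according to the standard waiting list". The Introduction describes the tests now pending at the centres as "with wait times exceeding 1 year".

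The Sample size section says that 12 months of full-time recruitment were funded. On missing data, the Statistical methods section says that "multiple imputation by chained equations will be considered for data missing at random when <20% of data is missing". The article gives no data cut for the delay outcome and does not say how patients still awaiting BPT enter the mixed model.

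**The concern.** A linear mixed model needs a number for each delay. A patient still on the list has only a lower bound, and the model cannot use it. If such patients were spread evenly over the two groups the harm would be limited, but the pathway puts almost all of them in the low-risk group. The delays lost are also the long ones. The low-risk mean is then too small and the contrast shrinks.

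The missing-data rule does not help. Even given the enrolment date, whether a delay is observed depends on its own length, so it is not missing at random. Chained equations fitted to completed delays could even impute a value shorter than the time the patient has already waited.

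At stake is the headline result. It would vary with the date on which the database is frozen, and it could disagree with the Kaplan-Meier and Cox results for the same outcome.

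**Working it through.** **The plan's own figure.** The article gives no figure for pending tests. Its only number near this outcome is the sample-size effect, Cohen's f = 0.07 with N = 1500, 5% alpha, 80% power and correlation 0.5. It states neither the number of groups k nor the number of measurements m. The noncentrality is λ = f²·N·m / (1 + (m−1)·0.5).
- k = 2, m = 1: λ = 0.0049 × 1500 = 7.35, power 0.773.
- k = 2, m = 2: λ = 0.0049 × 1500 × 2 / 1.5 = 9.8, power 0.879.
- k = 3, m = 2: power 0.806, which matches 80%.

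The calculation is for completed repeated measurements. The point here does not rest on it.

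**Inputs from the article.** Recruitment lasts 12 months. High-risk BPT follows in about 2–4 weeks. Spirometry is inconclusive in up to 80% of cases and over 60% in children (Introduction).

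**Assumptions.** Entry is uniform over 12 months. Half of patients are high-risk; the Introduction gives half for people with asthma, and this is extended to all referred patients. The low-risk wait from study visit to BPT takes four forms: fixed 13 months, gamma with mean 12, gamma with mean 6, or uniform 0–14 (mean 7). The data cut is 12 to 36 months after study start.

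**Formula.** Let p be the share with non-diagnostic spirometry, W the low-risk wait, h the high-risk wait (3 weeks, or 0.69 month) and F the share of needed low-risk BPTs done by the cut. The wait before the study visit is taken as alike in both groups and cancels.
- True difference = p·E[W] − p·h.
- Completed-case low-risk mean = p·F·E[W | done] / (1 − p + p·F).

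**By hand, W fixed at 13 months, p = 0.8.** The true difference is 0.8 × 13 − 0.8 × 0.69 = 10.40 − 0.55 = 9.85 months.
- Cut at 12 months: F = 0. The only completed low-risk delays are those diagnosed at spirometry, so the difference is about −0.5.
- Cut at 18 months: F = 5/12. Low-risk delays missing are 0.8 × 7/12 = 47%. The low-risk mean is 4.33 / 0.533 = 8.13, and the difference is 8.13 − 0.55 = 7.58, or 77% of true.
- Cut at 24 months: F = 11/12. Missing are 0.8 / 12 = 7%. The low-risk mean is 9.53 / 0.933 = 10.21, and the difference is 9.66, or 98% of true.

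**Simulation, 400,000 patients per scenario, p = 0.8.** Cells show the completed-case difference as a percentage of the true one, with the share of low-risk delays missing in brackets.

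| Low-risk wait | True difference (months) | Month 12 | Month 18 | Month 24 | Month 30 |
|---|---|---|---|---|---|
| Fixed 13 | 9.9 | -5% (80.0%) | 77% (46.5%) | 98% (6.8%) | 100% (0%) |
| Gamma, mean 12 | 9.0 | 25% (64.1%) | 57% (36.8%) | 79% (14.5%) | 92% (4.4%) |
| Gamma, mean 6 | 4.3 | 61% (39.3%) | 88% (7.7%) | 98% (0.6%) | 100% (0%) |
| Uniform 0–14 | 5.0 | 40% (45.7%) | 80% (15.3%) | 99% (0.9%) | 100% (0%) |

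With p = 0.6 the ranges are -5% to 51%, 49–86%, 76–98% and 90–100%. No scenario overstated the difference. High-risk delays missing were at most 4.7% at month 12 and none from month 18.

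**The 20% limit.** At month 12, 16.5–42.4% of all delays are missing, and six of the eight scenarios exceed 20%. By month 18 only one does (23.3%), so imputation would be open to consideration while the loss is still one-sided.

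**Another reading of the endpoint.** If the last test conducted is taken to be spirometry for a patient still awaiting BPT, nobody is missing, but the difference shrinks more. With gamma mean 12 at month 12 it is 0.5 months against a true 9.0; completed cases give 2.2.

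**The case against.** The strongest reply is that the bias needs an early data cut, and none is stated. A reader might infer that the study ends after 12 months and that the longest delays are bound to be lost. The documents do not support that. The 12 months are funded recruitment. Questionnaires run to 12 months after diagnostic confirmation (Study visits), so data collection outlasts recruitment. If analysis waits for every BPT, the bias vanishes. This stands, and it makes the size conditional. The article does not commit to such a wait, however, and the Setting section counts follow-up from the initial diagnostic visits instead.

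A reader might also infer that low-risk patients wait over a year after their study spirometry. The figure in the Introduction describes tests now pending, not that residual wait, and the Discussion expects study therapists to reduce the backlog. Nor are all low-risk patients exposed: those diagnosed at spirometry or referred directly for BPT have a complete delay at the visit.

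It would also be too strong to say that the plan imputes pending delays, or that it uses complete cases above 20% missing. It says only that imputation will be considered for data missing at random below that limit.

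Finally, Kaplan-Meier and Cox analyses are already planned and can handle censoring. That is correct, and the issue is their rank. The curves are an addition for display and the Cox model is for finding predictors, while the mixed model comes first. The error also runs against the study's hypothesis, so it threatens the size of the effect more than it risks a false claim of benefit.

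**Conclusion.** The point holds in conditional form. A mixed model of completed delays is biased towards zero whenever low-risk BPTs are pending at analysis. The imputation rule does not repair this, and the article does not rule the situation out. Across both assumed shares of non-diagnostic spirometry, the loss is severe at a 12-month cut (39% or more of the true difference). It is 12–51% at 18 months, about 1–24% at 24 months and 10% or less from 30 months. These figures rest on assumed waits with means of 6–13 months, uniform entry and equal risk groups. The direction rests only on the scheduling rule and the definition of the outcome. The documents do not support the stronger claim that the primary result will be understated by a known amount.

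**What to change.** Make a censoring-capable contrast from the time-to-event analysis already planned the primary one.
- **Estimand:** preferably the difference in restricted mean waiting time at a fixed horizon, stratified by centre. The horizon should lie within the follow-up available at the data cut.
- **Cox model:** keep the hazard ratio as supportive. Proportional hazards is doubtful when one group is tested within weeks and the other follows a long list.
- **Pending patients:** censor them at a stated data cut and do not impute their delays. State that spirometry does not close the delay of a patient still awaiting BPT.
- **Delayed entry:** participants come from an existing waiting list and the delay runs from requisition. Either use time from requisition with entry at enrolment, or count time from the study visit at which biomarkers are measured. State how patients diagnosed on the day of entry are counted.
- **Mixed model:** keep it as a supportive analysis, labelled as restricted to completed tests.

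Alternatively, keep the mixed model primary and fix the data cut after all study BPTs are complete.

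The cost is small but not only wording. The result is stated as a restricted mean difference. The sample-size statement, which rests on a repeated-measures ANOVA, should be restated for the new primary contrast. The alternative may cost a later analysis date.
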